### Data collection and management

Data will be collected in epicollect5 and analysed using Statistical Package for Social Sciences (SPSS) Version 25 (IBM Corp.). Department of Community Medicine and Family Medicine, All India Institute of Medical Sciences, Bhubaneswar, had more than 10 years of experience for data collection and data management in various studies which includes national and international collaborative studies and various trials. The standard guidelines will be followed for data entry, coding, and storage. Categorical variables will be presented as percentages or proportions. Continuous variables will be presented as mean and standard deviation. Intention to treat analysis will be done to evaluate the effectiveness of peer-led intervention compared to standard care. The multivariate analysis will be performed to adjust for confounders. For missing variables, the replacement will be tried, if essential, based on the characteristics and quantiles of the variables. There won’t be any interim analysis and no formal trial-stopping rule, as this is a behavioural intervention study with no anticipated problems detrimental to the participant.

The effect of the peer-led intervention will be estimated by Difference in Difference (DID) analysis. A *p*-value of less than 0.05 will be considered statistically significant.

The outcome assessor is not aware of the link with intervention. At the end of one year (12 months) following *outcomes* will be assessed:Improved control status of Non-communicable diseases (hypertension and/or diabetes mellitus and/or dyslipidaemia) in the intervention arm compared to the standard care arm.Mean reduction of blood pressure in the intervention arm compared to the standard care arm.Mean reduction in HbA1C among diabetes mellitus patients in the intervention arm compared to the standard care arm.Mean reduction of blood cholesterol in the intervention arm compared to standard care.

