### Trial design

This is a cluster randomized controlled parallel-group trial with a superiority framework. Village is a cluster in the study. Villages will be randomized to two study arms with a 1:1 allocation ratio. The participants in the intervention arm will receive a peer-led intervention model for six months in addition to standard care.

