### Sample size

The sample size was calculated using nMaster 2.0 software (https://www.cmc-biostatistics.ac.in/nmaster/) with the formula for cluster study design:

$$n=\frac{{\left({z}_{\frac{\alpha }{2}}+{z}_{1-\beta}\right)}^2\left[{p}_1\left(1-{p}_1\right)+{p}_2\left(1-{p}_2\right)\right]\left[1+\left(m-1\rho \right)\right]}{{\left({p}_1-{p}_2\right)}^2}$$where *p*1 = proportion of outcome in the experimental group

*p*2 = proportion of outcome in the control group

*α* = level of significance

1-*β* = power

*ρ* = Intra-cluster correlation coefficient

*m* = size of the cluster

Considering the proportion of outcome in the control group as 50%, an alpha of 5%, power of 90%, effect size of 20%, design effect of 2.5 and loss to follow-up as 20%, the estimated sample size was 720 participants (40 clusters with 18 participants in each cluster) (Supplementary file 01).

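### The only stated missing-data rule is discretionary quantile-based replacement; if applied once to lost 12-month outcomes, it would give too small a standard error or a distorted effect, depending on choices the protocol leaves open

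*Protocol article*

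**What the plan says.** Under Data collection and management, the Protocol article commits to an intention-to-treat comparison: "Intention to treat analysis will be done to evaluate the effectiveness of peer-led intervention compared to standard care". The same paragraph then gives its only rule for missing data: "For missing variables, the replacement will be tried, if essential, based on the characteristics and quantiles of the variables". The effect is to be estimated by difference in difference, judged at p below 0.05, with outcomes taken at 12 months. These are control status and the mean reductions in blood pressure, HbA1c and cholesterol.

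Under Sample size, the planning inputs are "Considering the proportion of outcome in the control group as 50%, an alpha of 5%, power of 90%, effect size of 20"% and "design effect of 2.5 and loss to follow-up as 20%, the estimated sample size was 720 participants", arranged as "40 clusters with 18 participants in each cluster". Under Trial design, allocation is by village: "Villages will be randomized to two study arms with a 1:1 allocation ratio". The baseline assessment paragraph has blood pressure, HbA1c and lipids measured in every participant.

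**The concern.** Three features of the rule are weak however the sentence is read.

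- **No trigger.** Replacement is to be attempted only where judged necessary, and nothing says who judges or when. The decision can be taken after outcomes are seen.
- **Best predictors not named.** The basis given is the features and quantiles of the variables. The sentence does not say that arm, the participant's own baseline value or village enters. Yet baseline is measured in everyone, the estimator is a change from baseline by arm, and village is the unit of randomisation.
- **No uncertainty.** Nothing in the rule lets the analysis distinguish a filled-in value from a measured one.

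At stake is the main comparison. If filled-in outcomes are counted as observed, the interval can be falsely narrow, or the estimate can be moved. Which of these happens depends on choices that the text leaves open.

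**Working it through.** **Inputs.** From Sample size: control proportion 0.50, absolute difference 0.20 (so 0.70 in the intervention arm), alpha 5% (two-sided, as the formula uses z at alpha/2), power 90%, design effect 2.5, loss 20%, 40 villages of 18. From Trial design: 1:1 allocation. Implied intra-cluster correlation: (2.5 − 1)/(18 − 1) = 0.088.

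**The plan's own figure.** (1.96 + 1.2816)² × (0.70 × 0.30 + 0.50 × 0.50)/0.20² = 120.8 per arm. Times 2.5 = 302.1. Times 1.2 for loss = 362.5 per arm, about 725 in total, against the stated 720. The inputs are therefore read as intended. At 20% loss, 360 per arm becomes 288 observed and 72 missing.

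**Continuous outcome, one replacement within arm, missing completely at random.**

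- *A constant such as the arm median:* the SD shrinks by √0.8 and 360 are counted instead of 288. Reported/true SE = √0.8 × √(288/360) = 0.80. Actual test level = 2 × [1 − Φ(1.96 × 0.80)] = 11.7%.
- *One random draw from the arm's observed values:* ratio = 1/√(1/0.8 + 0.2) = 0.83; level 10.4%.
- *Constant replacement at other missing rates:* 5% missing gives a level of 6.3%; 10% gives 7.8%; 30% gives 17.0%.

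**Continuous outcome, one replacement pooled over both arms.** Missing values in both arms come from the same source, so the missing fifth contributes no difference between arms. Expected estimate = 0.8 × true effect, a 20% dilution.

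**Check with clustering.** Simulation of a village-level t-test on a standardised 12-month outcome: 20 + 20 villages of 18, intra-cluster correlation 0.088, 20% missing completely at random, 6,000 runs per setting.

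| Handling | Reported/true SE (no effect) | Test level | Mean estimate of a true 0.40 SD |
|---|---|---|---|
| Observed data only | 0.985 | 5.2% | 0.398 |
| Median within arm | 0.786 | 11.7% | 0.402 |
| One draw within arm | 0.806 | 10.7% | 0.398 |
| Median pooled | 0.980 | 5.8% | 0.320 |
| One draw pooled | 0.987 | 5.1% | 0.320 |

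The simulation analyses the endline value rather than the change from baseline.

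**Binary control status, 50% versus 70%.** The median of a 0/1 variable is its more common category.

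- *Pooled:* the overall proportion is 60%, so missing becomes controlled. Intervention: 0.8 × 70 + 20 = 76%. Control: 0.8 × 50 + 20 = 60%. The difference reads 16 points.
- *Within arm:* intervention is again 76%. Control, sitting at one half, goes to 0.8 × 50 + 20 = 60% or 0.8 × 50 + 0 = 40%, depending on which side of one half the observed data fall. The difference reads 16 or 36 points.

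**The case against.** The strongest reply is that the sentence is vague rather than specific. It does not say that replacement is done once, does not mention the median, and does not say whether arms are pooled. It names characteristics as well as quantiles, and these could include arm or baseline. It speaks of variables, directly after a sentence on adjusting for confounders, so missing covariates are a fair reading. The 20% is an allowance in the sample size. Recruiting extra people to offset loss fits an analysis of those observed at least as well as one that fills in the lost. Further, the document is a condensed article, and a missing-data assumption, an imputation model and sensitivity analyses commonly sit in an analysis plan.

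Most of this stands, and it limits the point. A reader might infer that the plan commits to single imputation, disregards arm, replaces a fifth of the endline data and so understates the standard error. The documents do not support that chain. None of the first three is stated, and the links conflict: replacement that disregards arm is pooled replacement, under which the standard error is close to valid and the harm is dilution. Nor does the 11.7% carry over to binary control status, where the replacement shifts the proportions themselves.

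The appeal to an unseen analysis plan does not remove the point. The article is not silent here: it states a rule, and that rule leaves the trigger open and offers a poor basis for filling in outcomes. Missing outcomes are not excluded from it, and no other rule is given for an intention-to-treat analysis that expects loss.

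**Conclusion.** The point holds in conditional form. As written, the rule is discretionary, does not say that it uses arm, baseline or village, and carries no imputation uncertainty. If it is applied as a single replacement to missing 12-month outcomes at 20% loss:

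- within arm, a continuous outcome gets a standard error about 0.80 of its true value (0.83 for one random draw), and a nominal 5% test runs at roughly 10% to 12%;
- pooled, the test stays near 5% but the effect is diluted by about 20%;
- for control status, a 20-point effect could read as 16 or 36 points.

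These sizes assume data missing completely at random, 20% missing in each arm and the planning proportions. At 5% or 10% missing the within-arm inflation is much smaller. Loss related to disease control could add bias that is not quantified here. That the trial will in fact report too small a standard error cannot be concluded from the protocol.

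**What to change.** Delete quantile-based replacement for outcomes, and fix the method before any endline data are seen. Either of these would do:

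- a likelihood-based mixed model on all observed baseline and 12-month values with a village random effect (logistic for control status), in which the arm-by-time term gives the difference in difference; or
- multiple imputation carried out by arm, including baseline outcome and village.

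If replacement is meant only for missing covariates, say so and state when it applies. A sensitivity analysis that counts missing as not controlled is a reasonable option but not essential.

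The cost is a change of wording and a little more analysis work, with no added participants or visits. Intervals may be wider than under single replacement.

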**Fig. 3 Fig3:**
[figure not shown]
Sampling technique

*Cluster*: Forty villages will be selected randomly from the rural field practice area of AIIMS, Bhubaneswar.

*Participant*: The eligible population will be screened for hypertension, diabetes mellitus, and dyslipidaemia. The process of screening will be continued till 18 participants are recruited from each cluster.

*Baseline assessment*: A total of 720 (40*18) participants will be recruited at baseline after written informed consent. Anthropometry, blood pressure (BP), fasting blood sugar (FBS), post-prandial blood sugar (PPBS), glycosylated haemoglobin (HBA1C), lipid profile, and renal function test (RFT) will be done for all participants, in addition to interviews with NNDMS adult interview questionnaire. Standard guidelines as recommended by govt. of India will be followed for all measurements [21].

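### Difference-in-differences is less precise than baseline adjustment in this randomised trial, and the stated 90% power was not calculated for it

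*Protocol article*

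**What the plan says.** Under Data collection and management, the Protocol article names its effect estimator: "The effect of the peer-led intervention will be estimated by Difference in Difference (DID) analysis". The same section plans a multivariate analysis for confounders, without saying whether the baseline value of the outcome is among the covariates.

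Under Trial design, villages are randomised 1:1. The baseline assessment described under the sampling strategy includes blood pressure, and "glycosylated haemoglobin (HBA1C), lipid profile, and renal function test (RFT) will be done for all participants". The same people are reassessed at one year.

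Under Sample size, the trial is sized with a cluster version of the formula for two independent proportions. Its assumptions are: "Considering the proportion of outcome in the control group as 50%, an alpha of 5%, power of 90%, effect size of 20" per cent, then "design effect of 2.5 and loss to follow-up as 20" per cent. The result is: "the estimated sample size was 720 participants (40 clusters with 18 participants in each cluster"). The formula has one outcome proportion per arm. It has no baseline proportion and no correlation between baseline and follow-up.

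**The concern.** DID is built for settings where the groups may start from different levels. It subtracts each arm's baseline from its follow-up, so the whole of the baseline noise enters the estimate. Randomisation makes the expected baselines equal, so that subtraction is not needed to remove bias. Regression on baseline estimates how much of the baseline to subtract, and so does at least as well for any correlation up to 1.

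Two things are at stake. Precision is lost although the baseline data needed to recover it are already being collected. And the 90% quoted to justify 720 participants belongs to a different comparison from the one that will be made; whether DID has more or less power than 90% depends on a correlation that the protocol does not state.

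**Working it through.** **1. Reproduce the plan's figure.** Inputs from Sample size: control proportion 0.50; effect size 20%, read as an absolute difference, so 0.70 in the other arm; two-sided alpha 5% (z = 1.960); power 90% (z = 1.2816); design effect 2.5; loss to follow-up 20%.

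- n per arm = (1.960 + 1.2816)² × (0.70×0.30 + 0.50×0.50) / 0.20² = 120.8
- × 2.5 = 302.1
- × 1.2 = 362.5 per arm, 725 in total, against 720 stated.

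The figure reproduces as a plain comparison of two proportions. That the comparison is at follow-up is inferred from the allowance for loss to follow-up; the section does not define its outcome.

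**2. Compare the estimators.** Take a continuous outcome with equal variance at both times and correlation r. Relative to a follow-up-only comparison (variance 1), DID has variance 2(1−r) and ANCOVA has 1−r². Their ratio, ANCOVA over DID, is (1−r²)/[2(1−r)] = (1+r)/2.

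If the follow-up comparison has exactly 90% power, the power of another estimator with variance factor f is Φ[(1.960 + 1.2816)/√f − 1.960]. Example, DID at r = 0.3: f = 1.4, 3.2416/√1.4 = 2.740, 2.740 − 1.960 = 0.780, Φ = 0.782.

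| r (assumed) | DID factor 2(1−r) | ANCOVA factor 1−r² | ANCOVA/DID | DID power | ANCOVA power |
|---|---|---|---|---|---|
| 0.2 | 1.60 | 0.96 | 0.60 | 73% | 91% |
| 0.3 | 1.40 | 0.91 | 0.65 | 78% | 92% |
| 0.5 | 1.00 | 0.75 | 0.75 | 90% | 96% |
| 0.6 | 0.80 | 0.64 | 0.80 | 95% | 98% |
| 0.7 | 0.60 | 0.51 | 0.85 | 99% | 99.5% |

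DID always loses to ANCOVA for r below 1. Against the comparison that was sized, it loses below r = 0.5, ties at 0.5 and wins above it. Starting from 288 completers per arm (360 × 0.8) at design effect 2.5, the follow-up comparison has 88.6% power, DID has 76%, 89% and 98% at r = 0.3, 0.5 and 0.7, and ANCOVA has 91%, 95% and 99%.

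**3. Which r matters.** Villages are randomised, so the relevant r is that of village means. With 18 per village, a design effect of 2.5 implies an ICC of 1.5/17 = 0.088. The village component then makes up 18 × 0.088/2.5 = 0.635 of the variance of a village mean, so r ≈ 0.635 × (village-level correlation) + 0.365 × (within-village correlation). The documents give neither correlation. Assumed pairs show the spread:

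- village 0.5, within-village 0.3: r = 0.43, DID power 86%
- village 0.7, within-village 0.2: r = 0.52, DID power 91%
- village 0.8, within-village 0.3: r = 0.62, DID power 96%

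**4. Binary control status.** Variances need not be equal at the two times, so step 2 does not carry over exactly. As a check, assume 22% controlled at baseline (the Background quotes 21% for hypertension and 23.4% for diabetes) and 50% against 70% at follow-up, with 288/2.5 = 115.2 effective participants per arm. With no baseline–follow-up correlation, the DID variance sum is 2 × 0.22×0.78 + 0.46 = 0.803. The standard error is √(0.803/115.2) = 0.0835 and power is Φ(0.20/0.0835 − 1.960) = 67%. It rises to about 82% at a correlation of 0.3 and to at most about 89% at the largest feasible correlation. Baseline-adjusted power runs from 89% to 94%.

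**The case against.** DID is a legitimate estimator here. It is unbiased under randomisation, and it estimates directly the between-arm difference in mean reduction that most of the listed outcomes describe. The planned multivariate analysis might include baseline values, and covariate lists are commonly left to an analysis plan that is not shown. The sizing outcome is undefined: if it were the proportion of people whose control status improves, that proportion would already describe change and the mismatch would vanish for that one outcome. For control status, a logistic model with baseline adjustment estimates a conditional odds ratio, so the variance gains above would not transfer as they stand.

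Much of this stands, and it limits the point to efficiency and to a mismatch between sizing and analysis. It does not remove it. The article itself fixes DID as the estimator, and an unspecified adjustment for confounders does not replace it. Unbiasedness does not restore the lost precision.

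A reader might infer that the trial is underpowered. The documents do not support that: they give no r, and at a village-mean correlation of 0.5 or more DID matches or exceeds the power of the sized comparison for a continuous outcome. The low figures in the table hold only if village means are weakly correlated over the year. Nor do the documents support reading the choice of DID as a source of bias.

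**Conclusion.** The point holds as a matter of efficiency and reporting. Compared with baseline adjustment, DID needs 1.54, 1.33 or 1.18 times the information at r = 0.3, 0.5 or 0.7 (the inverse of 0.65, 0.75 and 0.85). This rests on a continuous outcome, equal variances at both times and the same design effect for both estimators. The direction holds for every r below 1; the size depends on an r that the protocol does not give.

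The stated 90% is the power of a two-proportion comparison without a baseline term. For DID the figure could be about 78%, 90% or 99% at the same three values of r, so it is unknown rather than shown to be inadequate. The change is worth making because it costs almost nothing.

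**What to change.** - Make the primary effect estimate the 12-month outcome regressed on arm and the baseline value of the same outcome, with a village random effect.
- For control status, adjust for baseline control status and report a risk difference or another effect scale named in advance.
- Keep DID as a sensitivity analysis.
- State under Sample size that the 90% refers to a comparison of two proportions without baseline adjustment.

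The village mean of the baseline value may be added, so that the model can fit a separate slope at village level. Block may be added too, though it was not a stratification factor. Both are optional.

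The cost is one changed sentence in the analysis section, a clarifying clause under Sample size and slightly more modelling. No new data are needed. The change should be made before outcome data are seen.

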### Adverse event reporting harms and post-trial care

Being a behavioural intervention, adverse events are not expected. Also, there is no anticipated harm and compensation for trial participation. In case of any incidental finding during the study, the participant will be linked to the nearest public health facility or AIIMS, Bhubaneswar.

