### Sequence generation

Computer-generated random numbers will be used for randomization by the primary investigator (PB). There will be no restriction or stratification. Out of 40 clusters, 20 will receive peer-led intervention and standard care. However, the other 20 clusters will receive standard care alone after randomization. Participants will be enrolled by an investigator (SD). After 1 year, the participants will be assessed in the same manner as the baseline (Fig. 1).

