### Intervention

The model will have six sessions (Fig. 2). The intervention will be delivered monthly through trained community health workers supervised by a physician. The sessions will be based on the following six domains: (1) NCDs self-care, follow-up care, risk factors and complications, (2) improving adherence to pharmacotherapy (linking with govt. hospital and/or janaushadhi), (3) community engagement for improving lifestyle modifications (physical activity and diet in NCDs), (4) importance of limiting substance use in NCD management, (5) Stress management, mental health, and yoga, (6) addressing other co-morbidities (cardiovascular conditions, hypothyroidism, cancer screening, etc.). Each peer group in the intervention arm will be provided with a glucometer with glucostrips and a sphygmomanometer. Peer groups will be encouraged to meet fortnightly. The participants will discuss with each other the challenges faced related to domains of intervention and seek appropriate guidance in monthly scheduled peer-led sessions. Through peer education “sharing experiences and learning among people with something in common”, the participants will be empowered to monitor blood pressure and blood sugar and identify feasible interventions for the peer group and individual level. Participants who adhere to lifestyle modifications and pharmacotherapy will be appreciated and share their stories with their peers. At the end of 1 year, intervention participants and the control group will be assessed again. Then the baseline and end line will be compared at individual and cluster levels. The participants in the control arm will receive standard clinical care at baseline [20] and be linked to the nearest govt. hospital for further follow-up care. There will be no special criteria for discontinuing or modifying allocated interventions. We are not storing samples or conducting any genetic or molecular analysis.

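### The harms section expects no adverse events because the intervention is behavioural, but the intervention targets drug adherence, diet and activity, and no equal capture of events in both arms is stated

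*Protocol article*

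**What the plan says.** The protocol article has a dedicated section, Adverse event reporting harms and post-trial care. It reasons from the type of intervention: "Being a behavioural intervention, adverse events are not expected". It anticipates no harm, and the one action it states is a referral: "In case of any incidental finding during the study, the participant will be linked to the nearest public health facility" or to the study institute. Data collection and management gives the same reason for having no interim analysis and no formal stopping rule.

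The Intervention section describes six monthly sessions. One domain is "improving adherence to pharmacotherapy (linking with govt. hospital and/or janaushadhi"), and another covers physical activity and diet. Each intervention peer group receives a glucometer and a sphygmomanometer, and "the participants will be empowered to monitor blood pressure and blood sugar and identify feasible interventions for the peer group and individual level". Control participants receive standard care at baseline and will "be linked to the nearest govt. hospital for further follow-up care". No trial contact with them between the two assessments is mentioned.

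On follow-up, Sequence generation says: "After 1 year, the participants will be assessed in the same manner as the baseline". The baseline assessment includes blood pressure, glucose measures and HbA1c, and it states that "lipid profile, and renal function test (RFT) will be done for all participants, in addition to interviews with NNDMS adult interview questionnaire". The four outcomes listed under Data collection and management are control status and mean reductions in blood pressure, HbA1c and cholesterol. For example, one is "Mean reduction in HbA1C among diabetes mellitus patients in the intervention arm compared to the standard care arm". All four measure benefit.

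**The concern.** The word behavioural describes how the intervention is delivered, not how it acts. If it works, participants take more of their antihypertensive and glucose-lowering treatment, and they eat and exercise differently. The route to lower blood pressure and HbA1c is also the route to symptomatic low blood pressure, hypoglycaemia and activity-related injury. The stated reason therefore does not support the stated expectation.

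The two arms also differ in how easily an event would come to notice. The intervention arm has monthly sessions for six months, is encouraged to meet fortnightly, and holds the devices. The control arm is linked to a hospital. Without a common question put to both arms, whatever is heard about events during the year will come mostly from the intervention arm.

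Two outcomes are possible at reporting. The paper may say that no harms occurred, which would restate the expectation. Or it may list spontaneous reports weighted towards the intervention arm, which could make the intervention look less safe than it is. The Discussion proposes integrating an effective model into the national programme, so a by-arm account would be useful.

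**Working it through.** **1. The texts side by side**

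| Point | Intervention arm | Control arm |
|---|---|---|
| Trial contact between assessments | Six monthly sessions; fortnightly meetings encouraged | None stated |
| Devices | Glucometer and sphygmomanometer per peer group | None stated |
| 12-month measurements | Same as baseline | Same as baseline |
| Stated question on events since enrolment | None | None |

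Very low readings or worse renal function at 12 months would be visible by arm, because everyone is measured. Symptomatic events, admissions and deaths during the year have no stated capture.

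**2. The plan's own sample size (Sample size section)**

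Inputs: control proportion 50%, effect 20 points, two-sided alpha 5%, power 90%, design effect 2.5, loss 20%.

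- Per arm before clustering, (z(α/2) + z(1−β))² × [p1(1−p1) + p2(1−p2)] / (p1−p2)² with 0.70 against 0.50: 120.8.
- Times 2.5: 302.1. Times 1.2 for loss: 362.5 per arm, 725 in total.

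The stated 720 (40 villages of 18, so 360 per arm) is reproduced closely. The article gives no figure on harms to reproduce.

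**3. What the added questions could show**

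Number answering per arm: 360 × 0.8 = 288.

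The design effect for harms is not given. I use 1 (no clustering), the planning value 2.5, and the value that the planning figures imply after loss:

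- Implied intra-cluster correlation, from 1 + (m−1)ρ = 2.5 at m = 18: 1.5/17 = 0.088.
- Answering per village: 18 × 0.8 = 14.4. Design effect: 1 + 13.4 × 0.088 = 2.18.

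One-sided 95% upper limit when no event is seen: 1 − 0.05^(1/n), with n the effective number.

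| Design effect | Effective n per arm | Upper limit |
|---|---|---|
| 1 | 288 | 1.03% |
| 2.18 | 132 | about 2.2% |
| 2.5 | 115.2 | 2.57% |

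The 95% half-width for the difference between arms is 1.96 × √(2p(1−p) × DE / 288), at assumed event rates p.

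| Assumed rate | DE 1 | DE 2.5 |
|---|---|---|
| 2% | 2.29 points | 3.62 points |
| 5% | 3.56 points | 5.63 points |
| 10% | 4.90 points | 7.75 points |

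This is a normal approximation and is rough at 2%. Half-widths of this size mean that the counts can describe the arms but cannot test a difference in safety with useful precision.

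**The case against.** **Detail may sit elsewhere.** A journal article usually leaves event forms and safety tables to the full protocol or analysis plan, and the interview questionnaire may contain relevant items. That stands as a limit. It does not remove the point, because the article has a harms section that takes a position and gives a reason, and the reason is open to challenge.

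**The label is accurate.** The trial supplies no drug and sets no dose, and supporting adherence to treatment prescribed elsewhere is behavioural. That is true. It does not follow that no events are to be expected from better adherence.

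**Care routes exist.** Sessions are supervised by a physician, participants seek guidance monthly, referral covers any incidental finding, and controls are linked to a hospital. A reader might infer that someone with symptoms or an abnormal reading has nowhere to go. The article does not support that, so no wider referral route is asked for. These are routes to care, though, and not records that can be compared by arm.

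**The harms are not documented.** The article names none and gives no rates, and it excludes people with diagnosed major complications and debilitated patients. A reader might infer that the intervention is unsafe or that a stopping rule is needed. Nothing in the document shows either.

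**Questions would not be perfectly fair.** Participants who have learned to monitor may report more mild events. That stands and is a cost of the fix. Nor are deaths protected from unequal capture: staff in regular contact with one arm would hear of deaths there sooner, so deaths need one common source.

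**Conclusion.** The point holds as a low-cost improvement. The stated reason for expecting no adverse events does not fit the intervention described. If the article is followed as written, a safety statement about the year would rest on an expectation or on unequal reporting.

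No harm rate can be derived from the document. The size of the point is what could be learned: with 288 answering per arm and no events, an upper limit of 1.0% without clustering and about 2.2% to 2.6% with it. This assumes the planned 20% loss, an effective-sample-size approximation, and a harms design effect no larger than the planning value. I give no limits for participants with diabetes, because their number is not stated and the design effect of 2.5 would not apply to so few per village.

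That the listed harms are plausible is a clinical judgement and not a finding from the document. Effectiveness estimates, tests and sample size are unaffected.

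**What to change.** 1. Reword the harms section: serious harm is not anticipated, but hypoglycaemia, symptomatic low blood pressure, and falls or activity-related injury may occur and will be recorded in both arms.
2. Add to the 12-month assessment a short fixed set of questions, identical in both arms, on hypoglycaemia, symptomatic low blood pressure, falls or injury, and hospital admission since enrolment.
3. Record deaths in both arms from the same source, the 12-month follow-up attempt, and not from what session staff happen to hear.
4. Report counts and percentages by arm descriptively. Any interval should allow for village clustering.

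The cost is about four interview items at a visit already planned, an entry for deaths, and rewording of the harms and follow-up text. Three weaknesses should be stated with the results: recall over 12 months is imperfect, answers are missing for those lost to follow-up, and mild events may be over-reported in the arm trained to monitor. No stopping rule and no change to the effectiveness analysis is needed.
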